**Enrollment**							
	Community consent	✓					
	Individual informed consent	✓					
	List other procedures	✓					
	Allocation		✓				
**Interventions**							
	AgF^b^			✓	✓	✓	
	AgF and KI^c^			✓	✓	✓	
**Assessments**							
	List baseline variables			✓^d,e,f^	✓^d,e,f^	✓^d,e,f^	
	List outcome variables	✓	✓	✓^d,e,f^	✓^d,e,f^	✓^d,e,f^	
	List other data variables				✓^g^		

^a^T1: enrollment.

^b^AgF: silver fluoride.

^c^KI: potassium iodide.

^d^DMFS: decayed, missing, and filled tooth surfaces.

^e^COHRQoL: child oral health–related quality of life.

^f^Dental anxiety.

^g^Focus group.

### Sample Size

We used the *power* command within Stata (version 15; StataCorp) and data on decay incidence, restorative outcomes, and COHRQoL impacts from the recently completed Kimberley study [6] to estimate the noninferiority sample size. Approximately 61% of the ART restorations were classified as successful (lesion arrestment), and 81% were estimated to be arrested with AgF treatment from published studies [19]; community intracluster correlation was 0.09. Using these parameters at 80% power and an α of .05 and with 30 clusters available (n=15, 50% clusters per treatment arm), the estimated sample size required was 180 in each arm. Allowing for a 25% loss to follow-up each year, the estimated sample size is 320 per arm or 22 children per cluster (rounded up). The sample size will also have 84% power to undertake subgroup analyses to detect a 20% difference in caries arrestment between carious lesions treated with AgF and KI or without KI. A sample size of 40 for the focus group interviews is expected to be sufficient to allow for the elicitation of parent perceptions about the care provided based on our earlier work [20,21].

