## Methods

### Trial Design

This study will use a robust, pragmatic, 2-arm parallel group cluster randomized, active-controlled, noninferiority trial design. This study will be reported according to the CONSORT (Consolidated Standards of Reporting Trials) guidelines on reporting of noninferiority trials [13]. Study communities will be randomized into test or control groups by a central study coordinator through a computer-generated block randomization procedure, stratified by expected decay experience and exposure to community water fluoridation levels based on findings from our earlier work in the Kimberley region [6]. Both arms of the study will be provided with dental care; the control arm will be treated using the ART and HT approach, and the test arm will be treated using AgF. The test group will be further randomized into 2 groups via computer-generated allocation in concealed envelopes at study sites to receive 1 of the 2 AgF formulations. One formulation will have 38% AgF and KI as a staining reducing agent (Riva Star Aqua; SDI Limited); the other formulation will have 40% AgF with stannous fluoride as a reducing agent (Creighton Dental AgF; Whiteley Corporation). The Riva Star Aqua group will be further randomized to receive KI or no KI to evaluate KI’s effect on reducing the staining associated with AgF and evaluate its impact on caries arrestment. Moreover, we will evaluate the COHRQoL [14] and child dental anxiety and undertake an economic evaluation of the interventions. Focus group interviews, using the yarning approach, will be conducted to better understand the impact of the dental treatments [12]. We will also test the effectiveness of teledentistry in caries diagnosis and treatment prescription. Participants will have digital images taken of their dentition with a smartphone using standardized procedures [15]. The images will be stored and sent securely to a calibrated assessor at a remote site. The assessor, blinded to group allocation, will evaluate the images and diagnose and prescribe treatment.

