**For Riva Star Aqua**
Remove food debris and plaque by brushing with a toothbrush (no toothpaste).Isolate teeth to be treated with cotton rolls and gauze and apply petroleum jelly to the gingiva and lips.Dry the affected tooth surfaces and at-risk tooth surfaces to be treated with cotton pledgets.Dispense 0.05 mL AgF; bend the microbrush applicator and dip the tip of the applicator into the agent.Apply the agent with the microbrush onto the decayed surface and rub gently, maintaining contact with the tooth for 60 seconds; apply the agent also to at-risk, non-decayed surfaces for 60 seconds and remove excess from all surfaces with cotton pledgets.For tooth surfaces assigned to receive potassium iodide (KI), dispense 0.1 mL KI; using a new microbrush, dip the brush tip into the agent and apply to the decayed surface until precipitate forms. Then, reapply the agent until no precipitate forms, with 5- to 10-second intervals between reapplications.Place Orabase adhesive (Colgate Oral Pharmaceuticals, Inc) onto AgF-treated decayed surfaces, with or without KI.Advise participant to refrain from eating or drinking for 30 minutes after treatment.

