### Assignment of Interventions: Allocation

#### Sequence Generation

Communities will be allocated to intervention or control groups through computer-generated block randomization, stratified based on the estimated caries prevalence and community water fluoridation levels within communities. Communities will be assigned to the intervention or the control group after receiving community consent. Individual children in the intervention group will be further allocated into AgF treatment or AgF and KI treatment via sealed envelopes containing computer-generated block randomization. The envelopes will be opened by the project coordinator at the community study site, and they will assign each child at enrollment.

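### The 84% power for KI versus no KI fits one split of the whole AgF arm, but Trial Design randomises only the Riva Star Aqua children to KI; the allocation sections conflict and the figure's basis is not stated

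*Protocol article*

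**What the plan says.** **Power claim.** The Sample Size section says "The sample size will also have 84% power to undertake subgroup analyses to detect a 20% difference in caries arrestment", the contrast being "between carious lesions treated with AgF and KI or without KI". It gives no group sizes, time point, number of lesions per child or within-child correlation for this comparison. The main calculation in the same section uses 61% arrest with ART, and "81% were estimated to be arrested with AgF treatment from published studies". It arrives at 180 evaluable children per arm, or 320 enrolled after allowing for 25% loss per year.

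**Allocation, nested version.** Trial Design randomises the test arm "to receive 1 of the 2 AgF formulations", and then: "The Riva Star Aqua group will be further randomized to receive KI or no KI". The intervention steps in Textbox 1 agree with this, because KI appears only in the Riva Star Aqua steps and the Creighton product is followed by stannous fluoride.

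**Allocation, two-way version.** Sequence Generation says: "Individual children in the intervention group will be further allocated into AgF treatment or AgF and KI treatment via sealed envelopes". Implementation repeats the two-way split. Neither mentions a formulation step. The interventions block of Table 1 also lists only AgF, and AgF with KI.

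**Unit.** Sequence Generation and Implementation assign the child. The KI step in Textbox 1 begins "For tooth surfaces assigned to receive potassium iodide (KI", which reads as assignment by surface.

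**The concern.** The nested and two-way descriptions give KI groups of very different size. If the power was computed for the two-way split but the trial runs the nested one, the KI comparison has about half the children that the figure implies.

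Trial Design makes the effect of KI on caries arrest an explicit question. If 84% power stands in the protocol, a non-significant result could be taken as good evidence that KI does not reduce arrest by 20 points, when the chance of missing such a loss may be much larger than 16%. Treating the Creighton children as further no-KI participants would recover numbers, but it would mix the effect of KI with that of formulation and stannous fluoride.

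The timing also matters. The envelopes have to be generated from one scheme, and recruitment is planned from March 2026.

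**Working it through.** **Inputs from the Sample Size section:** 180 evaluable and 320 enrolled per arm; 25% loss per year; arrest rates 61% and 81%; α 0.05. These are the ART and AgF rates, as no KI-specific rates are given. From an AgF rate of 81%, a 20-point difference can only run downwards, to 61%.

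**Assumptions:** two-sided test (sidedness is not stated), 1:1 at each split (ratios are not stated), and at first one lesion per child.

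**Formula.** For n per group and p̄ = (p1 + p2)/2:

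power = Φ{ [ |p1 − p2| − 1.96·√(2p̄(1 − p̄)/n) ] / √([p1(1 − p1) + p2(1 − p2)]/n) }

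**Step 1: reproduce the stated 84%.** One split of the evaluable arm gives 180/2 = 90 per group.
- 61% v 81%: (0.20 − 1.96 × 0.0676)/0.0660 = 1.02, power 84.7%.
- 60% v 80%: (0.20 − 1.96 × 0.0683)/0.0667 = 0.99, power 83.9%.

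Both agree with 84%.

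**Step 2: group sizes under Trial Design.**
- 24 months: 320 × 0.75 × 0.75 = 180; Riva half 90; KI split 45 v 45.
- 12 months: 320 × 0.75 = 240; Riva half 120; KI split 60 v 60.
- No loss at all: 320; Riva half 160; KI split 80 v 80.

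**Step 3: power for those sizes, one lesion per child.**

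| Groups | 61% v 81% | 60% v 80% |
|---|---|---|
| 45 v 45 (24 months) | 55.3% | 54.5% |
| 60 v 60 (12 months) | 67.9% | 67.0% |
| 80 v 80 (no loss) | 80.2% | 79.4% |

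For 45 v 45 at 61% v 81%: (0.20 − 1.96 × 0.0957)/0.0933 = 0.13, which gives 55.3%. With 45 per group, 80% power needs a difference of about 27 points below 81%.

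**Step 4: several lesions per child.** With m lesions per child and within-child correlation ρ, the effective number per group is 45m/(1 + (m − 1)ρ). These values of m and ρ are illustrations, not protocol figures (61% v 81%):
- m = 2, ρ = 0.3: 90/1.3 = 69.2, power 74%.
- m = 3, ρ = 0.5: 135/2.0 = 67.5, power 73%.
- m = 3, ρ = 0.3: 135/1.6 = 84.4, power 82%.
- m = 4, ρ = 0.3: 180/1.9 = 94.7, power 86%.

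Eligibility Criteria admit children without caries. They contribute no lesion to arrest, which lowers the effective number.

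**Step 5: pooling Creighton children as no KI.** 45 v 135 gives 71% to 76% at 61% and 81%, depending on which group has the lower rate. That is still below 84%, and KI is then confounded with formulation.

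**The case against.** The strongest counter-argument is about the unit. The power sentence speaks of lesions, not children, so 55% is not the power of the comparison as worded; with three or four lesions per child and a moderate correlation, 45 v 45 children could reach 82% to 86%. This stands as far as it goes: the true figure is undetermined. But the article gives neither quantity, so it does not support 84% by that route.

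Second, 90 v 90 is not the only route to 84%. The Riva half as enrolled, 80 v 80, gives 84% with a one-sided continuity-corrected test at 61% v 81%, or two-sided at about 65% v 85%. In addition, the main 180 per arm is reproduced with a continuity correction, and under that correction 90 v 90 gives only 80%. So 90 v 90 is the simplest match and not proof of what was done. The 80 v 80 routes, however, ignore the protocol's own 25% annual loss and use a one-sided test or rates that the article does not state.

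Third, Sequence Generation and Implementation omit the formulation step without excluding it, and the participant flowchart is not available here and may show the sub-arms. That is fair. The article's text still needs to agree with itself on sub-arms and unit.

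A reader might also infer that the staining objective lacks its claimed power. It does not follow: the third objective concerns discoloration, and the 84% is claimed only for caries arrest.

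**Conclusion.** The point holds in a limited form. The stated 84% fits a single split of the AgF arm and does not fit the nested scheme in Trial Design on the protocol's own evaluable numbers. Under that scheme, with 1:1 splits and one lesion per child, power at 24 months is about 55%, roughly 29 points below the claim, and about 68% at 12 months. More lesions per child would narrow or close the gap, by an amount that cannot be settled from the article.

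Two stronger readings are tempting. One is that the power simply is 55%; that would replace one unsupported number with another, since split ratios, lesions per child and within-child correlation are all unstated. The other is that the trial's sample size is wrong; the main AgF versus ART and HT calculation is untouched, because the KI contrast is described as a secondary comparison and a subgroup analysis. This should be fixed, but it does not threaten the main trial question.

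**What to change.** 1. Before the envelopes are produced, bring Trial Design, the KI step in Textbox 1, Table 1, Sequence Generation and Implementation to one allocation scheme. State the sub-arms, the ratio at each split, and whether child or surface is the unit.
2. If the nested scheme stands, replace the bare 84% with a power figure that states its group sizes, time point, arrest rates, sidedness, lesions per child and within-child correlation. Show about 55% (45 v 45 children, 24 months, 1:1 splits) as the one-lesion-per-child case, with about 27 points as the difference detectable at 80% power.
3. If the two-way scheme stands, state that the comparison is 90 v 90 evaluable children and explain where the formulation comparison fits.
4. Under the nested scheme, report the KI effect on arrest as an estimate with a confidence interval, compared within Riva Star Aqua children and not pooled with Creighton children.

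The cost is protocol wording and probably a less favourable power statement. No extra children are needed, but the change is easy only before allocation starts.

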### Recruitment

Strategies used in the recently (successfully) completed study in the Kimberley region will be adopted, with further community engagement undertaken to refine and develop the research protocol with the community leaders. Participant recruitment will commence after obtaining community consent to participate. Participant recruitment and retention strategies will include (but not be limited to) personal contacts by the project coordinator and the Aboriginal research assistant and engagement via the media (radio and television); website; local agencies, such as the community offices, the local school or schools, child care centers, community health and nursing centers; posters and flyers at local community stores, and word of mouth via the community and the AAC.

Parents of eligible children expressing an interest in participating will be provided with an information sheet, and the study will be explained by the Aboriginal research assistant. Upon receipt of signed consent, each parent will complete a questionnaire (the Aboriginal research assistant will assist the parent to complete the questionnaire). A calibrated examiner will then undertake the baseline clinical examination and take digital images of the dentition using a developed protocol.

After the baseline examination, each child will be offered treatment as per the protocol for the group allocation. Efforts will be taken to provide comprehensive care, including extractions. From experience, we found that concurrent treatment of the child after the baseline examination offered the best option for care and reduced the likelihood of nonattendance at subsequent appointments. In addition, where extra capacity to deliver dental treatment is available, we will provide dental care to children not enrolled in the study as a community service. The CONSORT participant flowchart is shown in Figure 1.

**Figure 1 figure1:**
[figure not shown]
Participant flowchart. AgF: silver fluoride; KI: potassium iodide.

### Assignment of Interventions: Allocation

#### Sequence Generation

Communities will be allocated to intervention or control groups through computer-generated block randomization, stratified based on the estimated caries prevalence and community water fluoridation levels within communities. Communities will be assigned to the intervention or the control group after receiving community consent. Individual children in the intervention group will be further allocated into AgF treatment or AgF and KI treatment via sealed envelopes containing computer-generated block randomization. The envelopes will be opened by the project coordinator at the community study site, and they will assign each child at enrollment.

#### Concealment Mechanism

The clinical team and the treating clinicians will be aware of the group assignment. Allocation assignment of KI after AgF application will be stored in opaque, sealed envelopes, which will be opened only at the time of treatment by the project coordinator.

#### Implementation

The allocation will be generated by the project lead off-site, and communities will be allocated into the intervention or control groups. Individual randomization will also be generated off-site and placed in sealed envelopes, which will be opened on-site by the project coordinator and assigned to AgF or AgF and KI treatment groups upon enrollment in the project.

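### Allocation concealment is weak as written: the generator of the community list is not separated from the study team, and a coordinator who also recruits opens the blocked KI envelopes at a time the protocol states in two ways

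*Protocol article*

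**What the plan says.** **Communities.** Sequence Generation describes the method: "Communities will be allocated to intervention or control groups through computer-generated block randomization, stratified based on the estimated caries prevalence", with water fluoridation as the second factor. On timing it says: "Communities will be assigned to the intervention or the control group after receiving community consent". Two sections name different roles. Trial Design: "Study communities will be randomized into test or control groups by a central study coordinator through a computer-generated block randomization procedure". Implementation: "The allocation will be generated by the project lead off-site, and communities will be allocated into the intervention or control groups". Eligibility Criteria limits the invitation to communities from the team's earlier study, and Trial Design bases the strata on that study's findings. Sample Size counts 30 clusters, 15 per arm.

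**Children in the test arm.** Sequence Generation: "Individual children in the intervention group will be further allocated into AgF treatment or AgF and KI treatment via sealed envelopes containing computer-generated block randomization". It continues: "The envelopes will be opened by the project coordinator at the community study site, and they will assign each child at enrollment". Implementation also ties assignment to enrollment. It says this list is made off-site but names no role for making it. Concealment Mechanism says the KI assignment stays in opaque envelopes that the project coordinator opens only when treatment is given. That is the only concealment device the article describes. Recruitment lists, among its strategies, "personal contacts by the project coordinator and the Aboriginal research assistant".

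**Openness.** The Blinding section says that participants, treating clinicians and assessors are not blinded.

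**The concern.** Concealment works when nobody who can influence entry knows, or can work out, the next assignment. Two features of the stated procedure weaken it.

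First, whoever generates a list knows it. If that person leads the team that approaches communities, and the team already knows each community's decay level, the order in which communities are brought to consent can be influenced by the arm that comes next. With 15 communities per arm, each one is 1/15 = 6.7% of its arm's clusters, so a few steered entries could matter for the main comparison of AgF with ART and HT.

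Second, a blocked list loses part of its unpredictability for anyone who sees each result in turn. Here that person is the project coordinator, who also has recruitment contact with families. If the envelope is opened before the baseline examination or the prescription of teeth, those steps could also be influenced by the assignment. The contrast at risk is AgF with KI against AgF without it.

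**Working it through.** The article states no figure for predictability, so there is none to reproduce. The check has three parts.

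**1. Who holds the community sequence.**
- Trial Design: a central study coordinator randomises.
- Implementation: the project lead generates the allocation off-site.
- Concealment Mechanism: covers KI only and gives no safeguard for the community list.

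On the Implementation text, the generator belongs to the study team, and nothing separates this role from community engagement. No passage says whether communities are randomised one at a time or together.

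**2. When the KI envelope is opened.**
- Sequence Generation and Implementation: at enrollment.
- Concealment Mechanism: only at treatment.
- Recruitment gives the order of steps as consent, questionnaire, baseline examination, then treatment. The Abstract adds that an oral health practitioner prescribes the teeth to be treated after the examination.

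On the enrollment text, the assignment may be known before examination and prescription. On the treatment text it is not. The two cannot both hold.

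**3. How much earlier envelopes reveal.** Assumptions, none of them stated in the article: 1:1 allocation, fixed block size B = 2k, and block boundaries known to the person guessing.

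Share of assignments that are certain once earlier ones in the block are seen = 1/(k + 1). For B = 4 there are six orderings. Two of them (AABB, BBAA) have two forced positions and four have one, so 8/6 = 1.333 forced positions per block, and 1.333/4 = 33.3%.

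Correct-guess rate when always naming the arm with fewer assignments so far in the block, with a coin toss at ties = [k + (2^(2k)/C(2k,k) − 1)/2] / (2k). For B = 4: [2 + (16/6 − 1)/2]/4 = 2.833/4 = 70.8%.

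| Assumed block size | Certain | Correct guesses |
|---|---|---|
| 2 | 50% | 75.0% |
| 4 | 33.3% | 70.8% |
| 6 | 25% | 68.3% |
| 8 | 20% | 66.6% |

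An unpredictable sequence gives 0% certain and 50% correct. A full enumeration of all blocks of each size gave the same values. Opening the envelope late does not change the table, because the information comes from envelopes already opened. It does limit what can still be influenced once the card is seen.

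**The case against.** **What stands**
- Communities are assigned only after they consent, so none can accept or refuse on a revealed arm. The pool is largely fixed (communities from the earlier study, 30 clusters available), which leaves limited room to choose who enters.
- Generating a list and carrying out randomisation can be separate tasks, so Trial Design and Implementation may describe two steps of one process. The article does not say so.
- The research assistant explains the study to parents. The coordinator's contacts are one of several recruitment and retention strategies. Teeth are prescribed by an oral health practitioner, not by the coordinator.
- An article may properly omit block size, and publishing it would weaken concealment. Its absence is no finding, and varied, undisclosed sizes may already be planned.
- Communities are stratified on caries and fluoridation, and Statistical Methods takes account of baseline factors. This offers partial protection.

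**Stronger readings that the documents do not support**
- That staff know upcoming KI assignments. The envelopes are opaque and sealed, the list is made off-site, and no passage says field staff see any list. At most, later assignments are partly guessable.
- That the project lead generates both lists. Only the community allocation is attributed to that role.
- A count of predictable children per community. Sequence Generation splits all test children by KI, whereas Trial Design splits only the Riva Star Aqua children. Nothing says whether the list restarts in each community.
- That children are recruited once their community's arm is known. Recruitment says only: "Participant recruitment will commence after obtaining community consent to participate". Assignment also follows community consent, and the order of the two is not fixed.

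**What it does not answer.** No safeguard is described for the community list, the two sections name different roles, and the envelope timing is contradictory. These are features of what the article states, not omissions of detail.

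**Conclusion.** The point holds as a weakness in the stated procedure, not as evidence that assignments are disclosed.

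At community level, a member of the team inviting communities with known decay levels may know the sequence, and the article describes nothing to prevent it. The effect on the AgF comparison cannot be sized from the documents. It depends on whether communities are randomised singly and on how much freedom there is in the order of consent.

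At child level, later KI assignments may be partly guessable: 50% to 20% certain for fixed blocks of 2 to 8 with known boundaries, and less if block sizes vary and are undisclosed. This can bias the KI contrast, which the article calls a secondary comparison and which lies within the test arm.

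The contradiction between opening at enrollment and opening only at treatment is plain on the text and rests on no assumption. The matter should be settled before the first community is randomised; recruitment is planned from March 1, 2026.

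**What to change.** 1. Reconcile Trial Design with Implementation by naming one person, with no part in community engagement or recruitment, to generate both the community list and the child-level list.
2. Randomise the consented communities in each stratum together, from coded IDs, so that there is no next community whose arm could be foreseen.
3. Reconcile Sequence Generation and Implementation with Concealment Mechanism, so that each KI envelope is opened only after consent, baseline examination and tooth prescription have been recorded for that child.

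Blocking of the child-level list can stay; this point does not call for an unblocked list.

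Cost: a change of who generates the lists, and text edits in four sections. The one practical downside is that all consents within a stratum must be in before that stratum is randomised, which may delay the first communities in it.
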